### Sample size

The total sample size is 1956 (489 in each of the four randomised groups). The sample size has been calculated using a median duration of mechanical ventilation of 7 days
^
4,
21
^ with a minimal clinically important difference of 1 day
^
22
^, resulting in a median duration of 6 days in the three intervention groups. This minimum clinically important value is also based on discussion with patient and family member advisors, who emphasised the importance of reducing time spent on the ventilator as a priority outcome
^
23
^. This median duration of mechanical ventilation and 1 day reduction treatment effect result in a hazard ratio of 0.86. Based on a log-rank test and at 90% power and a significance level of 0.05, this requires a sample size of 1856 (464 in each of the four randomised groups). Previous critical care trials have demonstrated low levels of loss to follow-up, at less than 5%
^
24–
28
^, and the nature of the proposed trial where all primary outcome data will be acquired whilst patients are in the ICU and identifiable to the research team, should minimise loss to follow up. Allowing loss to follow at the 5% level, requires a sample size of 1956 (489 in each of the four randomised groups).

As there is no clinical or biological rationale for, or expectation of, any interaction between the two mucoactives, the sample size has not been inflated for this purpose. This is in keeping with systematic review findings highlighting appropriate restriction of the factorial design to scenarios where treatments do not have the potential for substantive interaction
^
29
^.

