### Statistical methods

The primary analysis will be conducted on outcome data from all randomised patients according to the group to which they were allocated (i.e. intention-to-treat), regardless of the subsequent treatment they received. Trial results will be reported in accordance with Consolidated Standards of Reporting Trials guidance (CONSORT)
^
37
^. It is possible that some participants may not receive the full treatment dose, therefore a secondary per protocol analysis will be undertaken on the population who receive the complete treatment dose. Baseline characteristics, follow-up measurements and safety data, will be described using suitable measures of central tendencies; means and medians with the associated standard deviations, 95% confidence intervals, and interquartile ranges for continuous data; and frequencies and proportions for categorical data (including binary data). 

Primary outcomes for the randomised groups will be compared using a Cox proportional hazards model including site and adjusting for age and illness severity (APACHE II). For this analysis, no interaction between interventions will be assumed. Comparison for other continuous outcomes will use analysis of covariance to adjust for baseline characteristics and covariates. Comparison for binary outcomes will use generalised linear models (GLMs) as appropriate to estimate risk ratio and risk differences. 95% CI and p-value will be presented alongside the estimates. Analyses will be two-sided and tested at an
*a priori* significance level of p=0.05. The factorial design permits separate testing of the effects of carbocisteine and hypertonic saline on outcomes. Although there is no biologic rationale for, or expectation that, either mucoactive will have an effect on death, a sensitivity analysis for competing risk of death will be included. Sensitivity analyses will also be included to investigate the impact of any potential interaction between the interventions on the primary analysis, to investigate the impact of contamination between the interventions, and to investigate the impact of compliance on the primary analysis. 

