## Methods for additional analyses

Exploratory analyses for the primary outcome will be reported using interaction tests (treatment group by subgroup) and 99% confidence intervals for the following subgroups:

i)   Baseline APACHE II score

ii)   Baseline PaO
_2_/FiO
_2_ (PF) ratio

iii)   Pre-existing chronic respiratory condition prior to randomisation

iv)   Neurological diagnosis prior to randomisation

v)   Admission diagnostic categories; pulmonary vs. non-pulmonary

vi)   Receiving antibiotics for pulmonary infection at randomisation

The following Intercurrent Events have been identified which would prevent measurement of the primary outcome or change the interpretation of the measured primary outcome:

1.   Death prior to the timepoint at which randomised treatment is due to start

2.   (a) Hypertonic saline allocated in randomisation but not started

      (b) Carbocisteine allocated in randomisation but not started

3.   Death before successful unassisted breathing. 

4.   Transfer to another ICU before successful unassisted breathing. 

5.   Use of non-trial mucoactives 

6.   Patient withdrawal from intervention

Events 1, 2(a) and 2(b) are expected to be rare and no specific actions will be taken: analysis of these events will be by intention to treat, except for event 1 which will be handled in the same way as event 3. Event 3 will be treated as a competing risk for the primary outcome and will therefore be analysed using a hypothetical strategy. Event 5 will be dealt with using an intention to treat approach. Event 6 will also be handled using a hypothetical strategy, in which the time to unassisted breathing will be censored at the point of withdrawal and the withdrawals will be assumed to lead to missing at random data on the primary outcome. Complete follow-up should still be possible for most participants in whom event 4 occurs; if not, the hypothetical strategy used for event 6 will also be implemented.

Further details and a full description of all analyses are provided in the Statistical Analysis Plan available at
https://nictu.hscni.net/service/march-trial/march-trial-documents/).

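### The 1856 in the sample size is a log-rank event count used as a patient count, so 90% power depends on whether death counts as an event, which the article does not settle

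*Protocol article*

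**What the plan says.** All references are to the protocol article.

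**Sample size.** "The sample size has been calculated using a median duration of mechanical ventilation of 7 days", with a one-day difference "resulting in a median duration of 6 days in the three intervention groups". The section continues: "This median duration of mechanical ventilation and 1 day reduction treatment effect result in a hazard ratio of 0.86". Then: "Based on a log-rank test and at 90% power and a significance level of 0.05, this requires a sample size of 1856", which is 464 per group. A 5% allowance for loss to follow-up takes this to 1956 (489 per group). The section gives no number of events, no event proportion and no allowance for death. It does not say which group is the reference for the hazard ratio.

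**Death is treated in three places:**

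- *Outcomes, primary outcome:* the duration runs to successful unassisted breathing or death, with follow-up to 60 days. Death completes the outcome.
- *Statistical methods:* the primary analysis is a Cox model, and competing risk of death is left to a sensitivity analysis, on the ground that "there is no biologic rationale for, or expectation that, either mucoactive will have an effect on death".
- *Methods for additional analyses:* death before successful unassisted breathing is intercurrent event 3, and "Event 3 will be treated as a competing risk for the primary outcome", analysed under a hypothetical strategy. Death is then not an event.

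**The concern.** A log-rank test or Cox model draws its power from events, not from patients. A required number of events becomes a number of patients only after division by the expected proportion with an event. The article makes no such division, so it takes that proportion to be 1.

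That is harmless if nearly everyone reaches the event by day 60. It is not harmless if patients who die on the ventilator supply no event. The section on adverse events describes a population in a life-threatening situation and lists death among expected events, so the loss cannot be assumed to be trivial.

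At stake is the stated 90%, the yardstick against which a null result would be read. The interim analysis is also meant to check the sample size assumptions, yet the one that matters most here, the event proportion, is not written down.

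**Working it through.** **Inputs.** Hazard ratio 0.86, power 90%, alpha 0.05, medians 7 and 6 days, loss 5% (Sample size). Two-sided testing: "Analyses will be two-sided and tested at an" *a priori* level of 0.05 (Statistical methods). Each main comparison is half of all patients against the other half (Objectives). The proportion dying before unassisted breathing is not given; 10% to 40% is **assumed**.

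**1. Reproduce the plan's figure.**

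- Freedman: E = [(1 + HR)/(1 − HR)]² × (1.960 + 1.2816)² = (1.86/0.14)² × (3.2416)² = 1854.7. Rounded up to a multiple of four, this is 1856 = 4 × 464.
- Schoenfeld: E = 4 × (3.2416)² / (ln 0.86)² = 1847.7.
- Loss: 464/0.95 = 488.4, rounded up to 489; 489 × 4 = 1956.

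The stated figures are matched without dividing by an event proportion. One-sided versions (1506 and 1512) do not fit. With the unrounded ratio 6/7 = 0.857, the requirement is 1769 (Schoenfeld) or 1776 (Freedman).

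**2. No deaths.** With exponential medians of 7 and 6 days, the proportions still ventilated at day 60 are 2^(−60/7) = 0.26% and 2^(−60/6) = 0.10%. About 928 × 0.0026 + 928 × 0.0010 ≈ 3 of 1856 patients have no event. Power is 90% at HR 0.86 and 91% at 6/7. Without deaths, events and patients are practically the same.

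**3. Death is not an event.** Events are E = 1856 × (1 − d), where d is the share dying first. Power is Φ(√E × (1 − HR)/(1 + HR) − 1.96) by Freedman, or Φ(√E × |ln HR|/2 − 1.96) by Schoenfeld.

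| d (assumed) | Events | Power, HR 0.86 (Freedman) | Power, HR 6/7 (Schoenfeld) | Analysed patients for 1855 events |
|---|---|---|---|---|
| 10% | 1670 | 86.8% | 88.3% | 2062 |
| 20% | 1485 | 82.6% | 84.4% | 2319 |
| 30% | 1299 | 77.4% | 79.3% | 2650 |
| 40% | 1114 | 70.9% | 73.0% | 3092 |

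A log-rank simulation (3000 runs per setting, liberation HR 7/6, deaths censored, d set in the control group) gave 87%, 85%, 80% and 74%.

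The margin for deaths among 1856 analysed patients is almost nil at 0.86 (1855 needed) and 1 − 1769/1856 = 4.7% at 6/7.

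**4. Death is an event.** Nearly all 1856 patients then have an event by day 60.

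- *The medians describe the composite:* step 2 applies, and power is 90–91%.
- *The one-day effect acts on liberation only and death is unaffected (added assumption):* the composite hazard ratio is (1 − d) × 7/6 + d = 1.15, 1.13, 1.12 and 1.10. Power with 1856 events (Schoenfeld) is 85%, 77%, 66% and 54%.

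**5. Direction of the hazard ratio.** The event is coming off the ventilator. With medians of 7 (control) and 6 (intervention) and proportional exponential hazards, intervention v control is 7/6 = 1.17, or 1/0.86 = 1.16 from the rounded figure. The stated 0.86 is the ratio of medians. Both formulas give the same number of events for a ratio and its reciprocal.

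**The case against.** The strongest reply is that the sample size uses the outcome exactly as defined. The primary outcome ends at unassisted breathing or death, the Sample size section powers on the median of that same named duration, and so the 7 and 6 days already describe the composite. Almost every patient then has an event, and 1856 patients deliver 90%. This stands. A reader might infer that the trial lacks 90% power however death is handled; the documents do not support that.

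Three further points also stand in part.

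- The lowest figures (85% down to 54%) need the one-day effect to fall on liberation alone. The Sample size section does not say so. They show sensitivity to an unstated assumption and are not the trial's power.
- A reader might take "result in a hazard ratio of 0.86" to mean that the trial is designed around slower liberation, or that its size is wrong. Neither follows: no reference group is named, and inversion changes neither N nor power. It is a labelling defect.
- The 5% loss allowance gives some cushion if little of it is used. With no loss at all, 1956 patients and 5% deaths give 1858 events, which meets the requirement at 0.86; at 10% deaths there are 1760 events and power is 88.5%. But the article sets that allowance aside for loss, so it cannot also be counted on for deaths.

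The interim analysis at 978 patients is meant to check the sample size assumptions. It does not answer the point, because no event proportion is stated for it to be checked against.

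The composite reading also has a consequence the article does not disclose. If death is unaffected, a composite ratio of 7/6 at 30% deaths needs a liberation ratio of (7/6 − 0.3)/0.7 = 1.24. That bears on how plausible the target is, not on whether the power is delivered.

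**Conclusion.** The concern holds in conditional form. The 1856 is a required number of events entered as a number of patients, with an implied event proportion of 1.

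- Under the handling in Methods for additional analyses (death not an event), the stated 90% fails once deaths before liberation exceed about 5% at most, given 1856 analysed patients. Power is about 87–88%, 83–84%, 77–79% and 71–73% at 10%, 20%, 30% and 40% deaths. The ranges span HR 0.86 and 6/7.
- Under the literal outcome definition, with the medians read as those of the composite, 90% holds.

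The size of any shortfall rests on an assumed death range, because the article gives no rate. What is wrong as written is an unqualified 90% that fails under one of the article's own treatments of death, with nothing to say which treatment it was calculated for. The direction of the hazard ratio is a secondary correction.

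**What to change.** 1. Reconcile Outcomes, Statistical methods and Methods for additional analyses on whether death before unassisted breathing is an event, a censoring or a competing risk in the primary analysis. This comes first, because writing liberation events into the sample size would presuppose one answer.
2. Restate the Sample size section as about 1,855 required events of that type, and say which duration the 7 and 6 day medians describe.
3. Give the expected number of events among 1956 patients, using the event fraction pooled over all groups and not split by arm, and the power this yields. Trial status reports 1820 patients enrolled, so pooled data should be available.
4. Claim 90% only if that count and the matching effect support it.
5. State the target as intervention v control for time to coming off the ventilator: 7/6 = 1.17 (1.16 as the reciprocal of the rounded 0.86).

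The cost is a possibly less favourable stated power. No extra patients and no comparison between arms are required.

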### Recruitment

Recruitment for the MARCH trial will take place in at least 40 adult, general ICUs, across all four UK nations, that are able to care for Level 3 critical care patients
^
33
^. The ICUs must provide evidence that they have:

-   A proven track record of participating in ICU research

-   Access to the target population

-   Local PI willing to lead the trial at that site, with local trial team including medical, physiotherapy, and pharmacy representatives

-   Clinicians in the ICU who have clinical equipoise for use of mucoactives in this patient population and agree to maintain trial allocation in patients randomised by their colleagues

Staff must comply with the trial protocol, standard operating procedures (SOPs), the principles of Good Clinical Practice (GCP), regulatory requirements, and be prepared to participate in appropriate trial training. A training package will be provided to sites who participate in the study. A list of study sites is available from the study website (
https://nictu.hscni.net/service/march-trial/march-study-sites/).

## Trial procedures

The trial is managed by the Northern Ireland Clinical Trials Unit (NICTU).

### Consent process

All invasively mechanically ventilated patients in the ICU will be screened daily for eligibility. The outcome of the screening process and reasons for the non-enrolment of potentially eligible patients will be recorded on the MARCH trial screening log using the Screened, Eligible, Approached, and Randomised (SEAR) framework
^
34
^. In the absence of patient capacity to provide prospective informed consent due to clinical condition (critical illness), this will instead be sought from a Personal or Professional Legal Representative (PerLR, ProfLR respectively). The person taking informed consent will be GCP trained, suitably qualified and experienced, and have been delegated this duty on the delegation log.

A PerLR is defined as a person who is not connected with the conduct of the trial who is suitable to act as the legal representative by virtue of their relationship with the patient, and is available and willing to do so
^
35
^. The PerLR will be informed about the trial by the responsible clinician or a member of the research team and provided with a copy of the Participant Information Sheet (PIS). If the PerLR decides that they are willing to provide consent for their relative/friend/partner to take part, they will be asked to sign the PerLR consent form. If no PerLR is available in person or by telephone, a ProfLR may be approached to give consent. A ProfLR is defined as a doctor responsible for the medical treatment of the patient if they are independent of the study, or a person nominated by the healthcare provider
^
35
^. The doctor will be informed about the trial by the responsible clinician or a member of the research team and given a copy of the PIS. If the doctor decides that the patient is suitable for entry into the trial, they will be asked to sign the ProfLR consent form. 

Patients will be informed of their participation in the trial by the responsible clinician or a member of the research team, either within the ICU or acute hospitalisation period, when they regain capacity to understand the details of the trial. The responsible clinician or a member of the research team will discuss the trial with the patient and the patient will be given a copy of the PIS to keep. The patient will be asked for consent to continue to participate in the trial and to sign the consent to continue form. To inform and enable the collection of follow-up data, sites will be advised to send a letter to the participants General Practitioner (GP) to advise them of their participation in the MARCH trial. Further details are reported in the Trial Protocol (
2024_12_02_MARCH Protocol_Final V4.0, available at
https://nictu.hscni.net/service/march-trial/march-trial-documents/).

### Collection and use of biological specimens

Biological samples (sputum and blood) will be collected at sites giving agreement to do so, and with any necessary infrastructure in place to support. Consent for sample collection is a specific item detailed in the MARCH informed consent process; patients with suspected or confirmed COVID-19 disease will not have samples collected. Samples will be collected by trained staff at Baseline (Day 0), Day 3, and Day 7, and processed according to the locally available MARCH Sample Processing Guideline; where any sample cannot be collected, this will not constitute a protocol deviation. Samples will be labelled with the patient’s unique Participant Study Number, and after any local processing, will be stored at –80 °C until transfer to Queen’s University Belfast, where they will be further stored at –80 °C until analysis and beyond study completion. All necessary ethical approvals for analyses of samples, or any future study, will be secured prior to any investigation being conducted. 

### Withdrawal of consent

The ProfLR, the PerLR, or the participant may withdraw consent from the study at any time without prejudice. If consent is withdrawn this will be documented in the patient’s notes and in the CRF. The elements of the trial to be withdrawn (from the following possibilities) will be documented:

•   Mucoactive administration if ongoing

•   On-going data collection during hospital admission

•   On-going data collection following hospital discharge

•   Confirmation of vital status

If the patient or patient representative declines on-going participation, anonymised data recorded, and samples taken up to the point of withdrawal, will be included in the trial analysis unless the patient or patient representative requests otherwise. 

### Assignment of interventions: allocation

**
*Sequence generation*
**

Participants will be randomised using an automated web-based or telephone system (Centre for Healthcare Randomised Trials (CHaRT), University of Aberdeen, UK) via randomly permuted blocks in a 1:1:1:1 ratio to the four study groups. There will be stratification by recruitment centre.

**
*Concealment mechanism*
**

The randomisation sequence will be saved in a restricted section of the Trial Master File (TMF), which can only be accessed by the trial statistician and not those who enrol or assign interventions. To ensure allocation concealment, the randomisation for an individual patient will not be revealed to an appropriately trained and delegated member of the research team at their site until the patient has been recruited into the trial.

**
*Implementation*
**

After informed consent, patients will be randomised via an automated web-based or telephone system. Sites will be provided with trial specific randomisation guidelines. Randomisation will be completed by an appropriately trained and delegated member of the research team. Each patient will be allocated their own unique Participant Study Number during the randomisation process, which will be used throughout the study for participant identification on all data collection forms and questionnaires. An entry will be recorded in the patient’s medical notes noting enrolment into the study.

### Assignment of interventions: Blinding

MARCH is a prospective, randomised, open label, unblinded trial. Patients, healthcare providers, and outcome assessors, will not be blinded to the allocated intervention in this trial in order to reflect routine practice when mucoactives are (or are not) used in critical care
^
36
^. The trial statistician, who has no role in decision-making with regards the conduct of the trial, will be unblinded and this will also facilitate linkage with the Data Monitoring and Ethics Committee (DMEC). The remainder of the trial team will also be unblinded for the purposes of managing data collection, reviewing cases to assess protocol deviations, and to undertake pharmacovigilance duties. As the trial design is open label, there is no unblinding procedure.

### Data collection

To ensure accurate, complete, and reliable data are collected, the NICTU will provide training to site staff. All data for an individual patient will be collected and recorded in source documents and transferred onto a bespoke, web-based, electronic CRF for the study. A data dictionary, record of automatic and manual data queries, and a full audit trail will ensure data captured are consistent, reliable, and fully compliant with GCP and any other relevant regulatory requirements. For routinely collected clinical data the NHS record will be the source document. Patient identification on the CRF will be through their unique Participant Study Number, allocated at the time of randomisation. Data will be collected and recorded on the electronic CRF by the PI or designee as per the CRF submission guidelines. If the participant is transferred to another MARCH site, the PI or designated member of the site study team will liaise with the receiving hospital to ensure complete data capture as per CRF instruction. If this is not possible, the primary outcome will be collected as a minimum.

For the economic evaluation, health-related quality of life (HRQoL) will be measured using the EQ-5D-5L administered at the time of consent to continue, 60 days and 6 months. Resource utilisation data will be collected via questionnaires administered at 6 months. Where the patient has been discharged from hospital, questionnaires will be administered by post, telephone, or email by the NICTU. The participating site will provide the NICTU with contact details for the patient (including name, address and email) to enable the collection of follow-up data.

